##### Interviews (Week 12)

Participants and their caregivers are invited to complete semistructured interviews. Interviews are conducted either one-on-one or as a dyad, depending on the participant’s and caregiver’s preference, by trained members of the trial team who are not involved in delivering the intervention. A semistructured interview guide is followed, in which the interviewer asks a series of open-ended questions with follow-up probes to elicit detailed responses. The interviews aim to gain a deeper understanding of participants’ and caregivers’ experiences with the PA intervention, including what they liked and disliked, its acceptability (satisfaction), feasibility, barriers and facilitators to participation, and plans for continued or future engagement in PA. The Capability, Opportunity, Motivation, and Behavior (COM-B) framework informed selected questions in the interview guide [113]. In addition, questions explore participants’ and caregivers’ desire for ongoing access to the PA intervention and other PA opportunities—see the “Maintenance (Week 12, Week 24, and Week 52)” section. Multimedia Appendix 3 presents the semistructured interview guide. All interviews are audio-recorded using a Sony ICD-PX240 or Sony ICD-PX470 recorder and transcribed verbatim.

#### Adoption (Throughout)

Adoption is assessed by tracking referral sources. Differences in referral rates are monitored across channels (eg, referral vs self-referral) and between the 2 sites, Alberta Children’s Hospital and Stollery Children’s Hospital.

#### Implementation (Throughout)

Implementation is being evaluated using data on indices of feasibility, including intervention delivery time, trial delivery time, required expertise, cost, fidelity of intervention delivery, and adverse events. Feasibility is defined by participant retention in the trial (ie, completion of assessments), adherence to the PA intervention (ie, percentage of PA sessions attended out of those offered), overall percentage of missing data, and participants’ and caregivers’ perceptions of feasibility, which are collected via qualitative interviews. For intervention delivery, the time required for delivering the PA intervention, conducting PA assessments (including administrative tasks), health care provider referral time, and the costs associated with implementation (eg, delivery and administrative support costs) are being tracked. Fidelity refers to the extent to which the intervention is delivered as intended and is assessed by randomly selecting 10% of PA sessions for each participant. These sessions are recorded and reviewed by 2 trial team members (AW, [name], or [name]) who are not involved in delivering the PA or conducting assessments. Trial team members review the recorded sessions using an established checklist covering various categories, including safety, exercise tailoring and modifications, and adherence to the protocol. This process provides a percentage of sessions delivered as intended—meaning the PA program is followed with appropriate modifications, behavior change components are embedded, and delivery remains autonomy-supportive and tailored to each participant’s preferences. Fidelity checks also offer an opportunity to provide feedback to individual instructors if improvements are needed. Adverse events are tracked using a standardized reporting form capturing details such as date, timing, site/location, duration, severity, action taken, and outcome, following the Common Terminology for Adverse Events (CTCAE) version 5.0 [114]. Participants, caregivers, and exercise professionals may report adverse events; however, the responsibility for documenting each adverse event lies with the exercise professional and trial staff.

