### Purpose and Study Objectives

The co-primary aims of this trial are to (1) assess the effectiveness of the videoconference-delivered PA intervention on participants’ device-measured PA (primary effectiveness outcome), as well as secondary effectiveness outcomes including participant- and caregiver-reported PA and participants’ quality of life, symptoms, cognitive function, resource use, and physical fitness outcomes (ie, aerobic endurance, lower body flexibility, shoulder flexion range of motion, balance, functional mobility); and (2) assess implementation of the PA intervention and the trial through evaluating recruitment, indices of feasibility, delivery time, expertise, cost, fidelity of intervention delivery, and adverse events.

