The resulting 12-week PA intervention, delivered via videoconference, includes sessions offered 3 times per week for 15-45 minutes and incorporates a combination of aerobic, resistance, balance, core, and flexibility exercises. Videoconference delivery allows participants to join whether they are at home or in the hospital. The intervention is tailored for each participant based on the frequency (ie, how often each exercise is completed and the number of PA sessions per week), intensity (ie, the difficulty of exercises or PA sessions), time (ie, duration of each exercise and each PA session), and type of exercise (ie, aerobic, resistance, balance, core, and flexibility). Each aspect of the intervention is modified based on participants’ needs, preferences, medical factors, age, and abilities, including how they are feeling and managing treatment-related side effects, their treatment schedules, and other considerations (eg, school or extracurricular commitments). PA sessions are provided regardless of whether participants are in the hospital or at home. Select behavior change techniques (eg, goal setting, feedback and monitoring, social support, self-monitoring) are embedded within PA sessions and discussed in an age-appropriate manner. Behavior change topics are also selected based on participant choice and ongoing conversations throughout the PA sessions. As noted above, participant autonomy is prioritized throughout. See Multimedia Appendix 2 for an overview of the PA intervention. Of note, caregivers are required to be present for each PA session, either at home or in the same room as the participant, depending on the participant’s age, functional characteristics, and preferences (see the “Safety” section). If caregivers wish, they may participate in the PA sessions after completing the Get Active Questionnaire to ensure readiness and safety for engaging in PA, although the primary focus remains on the participant [78].

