### Data Analysis

Data will be analyzed and disseminated through conference presentations and manuscripts at multiple time points, including interim and trial cessation. To date, interim analyses have been conducted covering implementation metrics within the first 30 months, descriptive information, and individual changes in selected secondary outcomes pre- to postintervention [117]. No predetermined stopping rules were set within the context of the interim analyses.

At trial cessation, the full dataset will be analyzed. Single proportion inference tests and CIs will be used to determine the proportion of eligible participants who provided informed consent (or assent where appropriate) and adherence rates to the intervention components. Initial plans to analyze effectiveness data included generalized linear mixed models to examine changes over time in participants’ device-measured PA (primary effectiveness outcome) and in secondary effectiveness outcomes, multilevel modeling to examine site differences in relation to the primary and secondary outcomes, and inclusion and stratification of covariates (sex, gender, and other factors) to explore changes between cancer and blood disorder diagnoses and across age ranges (if sufficient power). Given the information presented in the “Sample Size” section, this trial is well below the sample size target. Thus, at trial cessation, alternative data analysis approaches will be considered. It is anticipated that the analysis will emphasize individual (idiographic) patterns and trajectories rather than relying solely on the more aggregated approach described above. Implementation data related to reach (referral rate, participation rate, participant personal and medical information, caregiver personal information, proportion of participants from rural vs urban locations), adoption (sources of referrals, differences in referrals across referring sites), implementation (trial retention, adherence to the PA intervention, percentage of missing data, intervention delivery time, expertise, PA session fidelity, trial delivery time, adverse events), and maintenance (participants’ and caregivers’ desire for ongoing access to the PA, participant- and caregiver-reported PA levels at follow-up time points) will be assessed using descriptive statistics via SPSS (IBM Corp) or R (R Foundation). The CONSORT diagram ([60]; Figure 1) will be completed to illustrate participant recruitment and retention in the trial.

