## Results

This trial received funding in April 2022, and funding extensions were sought (due to slower and lower than anticipated recruitment) until March 2026. Participant recruitment commenced in March 2022 and will conclude in December 2025. Interim analyses were conducted in February 2025 and submitted in November 2025 [117]. As of October 2025, 105 patients have been referred (health care provider referral; n=90, 85.7%) or self-referred (n=15, 14.2%). Of the 105 referred participants, 42 (40%) scheduled a phone call with the trial team to receive more information, of which 26 (62%) provided informed consent; 16 enrolled in and completed the intervention, and 1 is currently actively in the intervention.

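### A single-proportion CI for session attendance would overstate precision to the extent that attendance clusters within children; the child should be the unit

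*Protocol article*

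**What the plan says.** The Implementation (Throughout) section makes adherence one of the indices of feasibility and defines it as "adherence to the PA intervention (ie, percentage of PA sessions attended out of those offered". The definition is a percentage. No level is given at which a child would count as adherent.

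The Data Analysis section states the inferential method in one sentence: "Single proportion inference tests and CIs will be used to determine the proportion of eligible participants who provided informed consent", continuing to "adherence rates to the intervention components". One method is thus assigned to two quantities. Later in the same paragraph adherence appears again, in a list of items for descriptive statistics: "implementation (trial retention, adherence to the PA intervention, percentage of missing data".

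On the number of sessions, The Intervention section says the programme "includes sessions offered 3 times per week for 15-45 minutes" over 12 weeks, and it lists among the tailored features "frequency (ie, how often each exercise is completed and the number of PA sessions per week". On the number of children, Results reports that "16 enrolled in and completed the intervention, and 1 is currently actively in the intervention". Adherence falls under the second co-primary aim, which is to "assess implementation of the PA intervention and the trial through evaluating recruitment, indices of feasibility".

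**The concern.** A single-proportion test or CI needs independent yes/no observations. Consent supplies them, with one answer per eligible patient. Adherence as defined does not: the yes/no event is attendance at a session, and each child supplies many sessions. The Intervention section itself says delivery is shaped by side effects, treatment schedules and other commitments. These differ between children and persist within a child, so some children are likely to attend most sessions and others few.

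If the sessions are counted as independent, a trial of about 17 children is reported as though it held several hundred observations. Recruitment is far below the target of 76, so the feasibility results are likely to carry much of what the trial can report. An adherence rate with a falsely tight interval would invite more confidence than the data give.

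**Working it through.** The article states no adherence figure, CI width or precision target, so there is no figure of the plan's to reproduce. The target of 76 concerns step counts and does not bear on this point.

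**Inputs from the article**
- Sessions per child: 3 per week × 12 weeks = 36. This is a ceiling, because the weekly number is tailored.
- Children: 16 completed + 1 active = 17 (October 2025).
- Sessions at most: 17 × 36 = 612.

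**Assumptions (not in the article)**
- True attendance 80%.
- Within-child correlation (ICC) between 0.05 and 0.5.
- Equal numbers of sessions per child.

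**Interval from pooled sessions.** 1.96 × √(0.80 × 0.20 / 612) = 0.032, or ±3.2 points.

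**Allowing for clustering.** The design effect is DEFF = 1 + (m − 1) × ICC, with m sessions per child. The pooled standard error is too small by a factor √DEFF. The half-width with the child as unit is t(0.975; 16 df) × √(0.80 × 0.20 × DEFF / 612), with t = 2.12. The approximate coverage of the pooled nominal 95% interval is 2Φ(1.96/√DEFF) − 1.

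At m = 36:

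| ICC | DEFF | SE too small by | Equivalent independent sessions | Child-level half-width (points) | Coverage of pooled 95% CI |
|---|---|---|---|---|---|
| 0.05 | 2.75 | 1.7 | 223 | 5.7 | 76% |
| 0.10 | 4.5 | 2.1 | 136 | 7.3 | 64% |
| 0.20 | 8.0 | 2.8 | 77 | 9.7 | 51% |
| 0.30 | 11.5 | 3.4 | 53 | 11.6 | 44% |
| 0.50 | 18.5 | 4.3 | 33 | 14.7 | 35% |

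**Simulation check.** In a beta-binomial simulation (40,000 runs, 17 children × 36 sessions, 80% attendance), the pooled interval covered 75%, 63%, 49%, 42% and 33% across the same ICCs. A t interval on the child percentages covered 94%, 94%, 93%, 93% and 92%.

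**Fewer sessions.** At m = 12 there are 17 × 12 = 204 sessions and the pooled half-width is ±5.5 points. DEFF is 1 + 11 × 0.05 = 1.55 at the low end and 1 + 11 × 0.5 = 6.5 at the high end, so the standard error is too small by 1.2 to 2.5 times. Approximate coverage of the pooled interval is 88% to 56%.

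The factor √DEFF depends on sessions per child and the ICC, not on the number of children. A few more children before recruitment closes would not change it.

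**The case against.** The strongest case on the other side is that the article never states its unit of analysis. It names a family of methods in one sentence and gives no null value for the test, so the sentence may be shorthand. A fuller analysis plan could classify each child as adherent or not and take an exact interval on the number of children, which would be valid. The wording also differs: the inferential sentence speaks of "adherence rates to the intervention components", while the phrase used in the definition recurs only in the descriptive list ("implementation (trial retention, adherence to the PA intervention, percentage of missing data").

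Much of this stands. A reader might infer that the protocol prescribes pooling sessions; it does not say so. A reader might also infer that this CI is the only account of uncertainty planned for adherence. The descriptive listing does not support that, since descriptive statistics on child percentages could well include a spread.

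It does not remove the point. The article defines only one adherence measure, and under that definition the session is the only yes/no unit. The child-level reading needs a cut-off the article does not give. The descriptive listing does not withdraw inference that the article says will be used. The later remark that alternative analyses will be considered follows on from the effectiveness models.

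The objection to the size is also fair in part. Attendance and ICC are assumed and 36 is a ceiling. If the number of sessions offered is already adjusted to a child's treatment, some of the clustering may be absorbed by the denominator, so the high ICCs are the less secure end.

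**Conclusion.** The point holds as a mismatch between a stated method and a defined measure. Applied to sessions, which is the natural but inferred reading, the single-proportion interval would be too narrow whenever attendance clusters within children. For ICCs of 0.05 to 0.5 the understatement of the standard error runs from about 1.7 to 4.3 times at 36 sessions per child and from 1.2 to 2.5 times at 12. It vanishes only if the ICC is near zero.

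The coverage figures are scenarios under assumed ICCs, not properties of this trial. It would go too far to say that a feasibility conclusion will be wrong: no threshold or decision rests on the adherence rate, and the step-count outcome is untouched. What is at stake is the honest precision of one feasibility index under a co-primary aim.

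**What to change.** Keep the single-proportion method for consent. For adherence, compute attended/offered for each child, report the distribution of those percentages, and give a 95% CI for their mean with the child as the unit (t interval, bootstrap or beta-binomial model). If the team in fact intends a per-child classification, it should state the cut-off before analysis and use an exact interval with children as the denominator.

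No new data are needed, since the attended and offered counts already underlie the percentage. The main cost is a wider interval: at 80% attendance and 36 sessions, about ±5.7 to ±14.7 points instead of ±3.2. With so few children the t interval itself covers slightly under 95% (92% at ICC 0.5 in the simulation), which is far closer than the pooled interval (33%). Where children are offered different numbers of sessions, the mean of the child percentages will differ somewhat from the overall percentage of sessions attended, so the report should say which is shown.

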#### Maintenance (Week 12, Week 24, and Week 52)

Maintenance is assessed via semistructured interviews—see the “Interviews (Week 12)” section—to explore participants’ and caregivers’ desire for ongoing access to the PA intervention or plans (or both) for continued engagement in PA. In addition, participant- and caregiver-reported PA levels will be collected at follow-ups through the m-GLTEQ via REDCap, enabling exploration of sustained PA levels.

### Quality Improvement Cycles

Quality improvement cycles are one way to explore and refine implementation strategies so that, by the end of the trial, there is an optimized approach (including all required resources; [115]). Within this trial, the Consolidated Framework for Implementation Research has been fully operationalized and is used to categorize the data collected [116]. Quality improvement cycles are conducted every 6 months, during which the trial team reviews participants’ and caregivers’ personal and medical information, as well as intervention fidelity data, to ascertain the necessity of potential additional recruitment strategies to further diversify the sample. Additionally, a purposefully recruited subset of health care providers and exercise professionals who have been involved with the intervention and trial are selected to participate in 1:1 semistructured interviews, based on their role in referring to or delivering the PA intervention, respectively. These interviews are not conducted during every quality improvement cycle but are scheduled based on conversations among the trial team. Additional individuals are recruited during quality improvement cycles when there have been new health care providers who have referred, and exercise professionals involved in PA session delivery or conducting assessments of physical function (or in both scenarios). Interviews are conducted by trained members of the trial team who are not involved in intervention delivery. A semistructured interview guide is followed. The interviewer asks a series of open-ended questions, with follow-up probes, to gain a better understanding of whether additional resources are required to facilitate recruitment or whether further training is needed to support the delivery of the intervention by the exercise professionals. The semistructured interview guide can be found in Multimedia Appendix 3. All interviews are audio-recorded using a Sony ICD-PX240 or Sony ICD-PX470 recorder and transcribed verbatim. Data from quality improvement cycles are analyzed using descriptive statistics, examining recruitment rates and participants’ personal and medical information (eg, sex, gender, and other factors), as well as content analysis for interviews. These data are being used to optimize implementation by exploring whether additional resources are required to support recruitment (eg, posters, brochures, emails), to support health care providers to refer, and whether further training is needed to support exercise professionals.

Any modifications identified during quality improvement cycles are carefully considered by the trial team and advisory board (see the “Participant and Caregiver Involvement” section) and are implemented only when deemed necessary to enhance recruitment, increase participant diversity, support health care provider recruitment, or improve training for trial staff and the exercise professionals (or in all of the aforesaid scenarios). No modifications are made to PA session delivery, assessments of physical function, or other aspects of the intervention or trial that could influence effectiveness data.

### Participant and Caregiver Involvement

Participants’ and caregivers’ perspectives are deemed critical within this work. As such, an advisory board was developed 1 year into the trial, in August 2023, after several participants had completed the intervention. Currently, the advisory board comprises 1 participant (of note, initially 2 past participants comprised the board; however, 1 passed away), 2 caregivers, 1 health care provider, 1 community partner, and 4 trial team members (including the 2 coprincipal investigators). The advisory board meets quarterly by videoconference to discuss data collected in the quality improvement cycles (when relevant), provide advice regarding potential challenges, gaps, and opportunities within the PA intervention and trial implementation, advise on current and future dissemination opportunities, and contribute to adaptation and scaling discussions. At trial cessation, advisory board members will have the opportunity to review and comment on all data and will work with the trial team to contextualize the findings. All members have also contributed to, reviewed, and approved this manuscript.

### Data Analysis

Data will be analyzed and disseminated through conference presentations and manuscripts at multiple time points, including interim and trial cessation. To date, interim analyses have been conducted covering implementation metrics within the first 30 months, descriptive information, and individual changes in selected secondary outcomes pre- to postintervention [117]. No predetermined stopping rules were set within the context of the interim analyses.

At trial cessation, the full dataset will be analyzed. Single proportion inference tests and CIs will be used to determine the proportion of eligible participants who provided informed consent (or assent where appropriate) and adherence rates to the intervention components. Initial plans to analyze effectiveness data included generalized linear mixed models to examine changes over time in participants’ device-measured PA (primary effectiveness outcome) and in secondary effectiveness outcomes, multilevel modeling to examine site differences in relation to the primary and secondary outcomes, and inclusion and stratification of covariates (sex, gender, and other factors) to explore changes between cancer and blood disorder diagnoses and across age ranges (if sufficient power). Given the information presented in the “Sample Size” section, this trial is well below the sample size target. Thus, at trial cessation, alternative data analysis approaches will be considered. It is anticipated that the analysis will emphasize individual (idiographic) patterns and trajectories rather than relying solely on the more aggregated approach described above. Implementation data related to reach (referral rate, participation rate, participant personal and medical information, caregiver personal information, proportion of participants from rural vs urban locations), adoption (sources of referrals, differences in referrals across referring sites), implementation (trial retention, adherence to the PA intervention, percentage of missing data, intervention delivery time, expertise, PA session fidelity, trial delivery time, adverse events), and maintenance (participants’ and caregivers’ desire for ongoing access to the PA, participant- and caregiver-reported PA levels at follow-up time points) will be assessed using descriptive statistics via SPSS (IBM Corp) or R (R Foundation). The CONSORT diagram ([60]; Figure 1) will be completed to illustrate participant recruitment and retention in the trial.

All interviews will be transcribed verbatim, and transcripts will be managed and analyzed in NVivo (Lumivero) using conventional content analysis [118]. Each transcript will be read several times so the authors conducting the analysis can familiarize themselves with the data. Next, the transcripts will be coded. Labels (ie, codes) will be created to reflect key ideas. Codes will then be organized into groups and higher-order categories [118]. Interviews with participants and caregivers will be analyzed to explore participants’ and caregivers’ experiences within the intervention; acceptability, barriers, and facilitators to participation; feasibility; and their desire for ongoing access to the PA intervention, plans for continued engagement in PA; or all of these.

With respect to integrating quantitative and qualitative data, the initial plan included an embedded mixed-methods approach. Quantitative data will be reviewed, and qualitative data will be layered over to expand and provide further context to the situation, thereby complementing the findings [119]. This integration is an important component of mixed-methods research and will provide a more comprehensive understanding of the effects of the intervention, enhancing the depth and context of the findings [120]. Should the target sample size not be met, as noted above, the embedded mixed-methods approach may shift to feature the qualitative data; this will be determined via consultation with the trial team.

Additional analyses of selected trial data are planned and will cover health care providers’ experiences referring and not referring to the IMPACT intervention and trial, as well as exercise professionals’ experiences delivering the 1:1 PA sessions, conducting assessments of physical function, or both. These data will be analyzed using the fully operationalized Consolidated Framework for Implementation Research and conventional content analysis. These analyses will be conducted and published separately from the main trial results. Finally, given the amount of data collected within this trial, additional exploratory analyses may be conducted; these analyses will seek to answer additional research questions and will occur only after the interim and main analyses described above, based on discussion and agreement among the trial team.

